#### Data management

The HSRC Sweetwaters team has successfully used mobile phones for data collection on several large scale evaluations and projects, including the Uthando Lwethu Study. Mobile phones will be used to collect all operational and research data through the mobile phone application by Mobenzi Researcher (Durban, South Africa). Data are temporarily stored in a non-readable encrypted file on the handset until an area with network coverage is reached and the data are uploaded to a secured server at the HSRC Sweetwaters site and removed from the mobile phone. Data security is enhanced by authentication protocols.

Participants’ names will not be associated with any physical or digital data collected or managed by the study, only research identification numbers will be used. Any tracing or other contact information, including signed consent forms will be stored separately from survey data and all records will be stored in locked file cabinets in study offices at HSRC. The files linking research identification numbers and names will be stored in a separate locked file cabinet, and a computer file only accessible by the Project Director, PI and Co-Is; and all computers will be password protected.

#### Adverse event reporting

All safety-related risks will be monitored routinely during data collection visits and intervention sessions. Any incidents involving subject safety will be reported by the PI to both institutional ethics committees (Human Sciences Research Council and University of Southampton) within 10 working days. The report will include information on 1) all serious adverse events associated with study procedures and/or 2) any events or problems involving the conduct of the study or patient participation, including problems with the recruitment or consent processes.

#### Impact of the COVID-19 pandemic

The COVID-19 pandemic has been a challenge for the Igugu Lethu study. Recruitment was scheduled to start April 1st, 2020, when South Africa declared a State of Disaster on March 15th, 2020. Initial restrictions on international travel, public gatherings and daily curfews were followed by a strict lock-down from 26th March 2020, resulting in study recruitment beginning in December 2020. With the various and continued COVID-19 pandemic restrictions and impacts, the study team have needed to repeatedly revise operational management to protect staff and participants. When all public gatherings were banned, the study team tried unsuccessfully to organise online group sessions with couples. Only 9% of the couples in our study report that both partners own a smartphone. Alternative arrangements such as lending smartphones to participants or using audio conferencing equipment to gather couples together were not feasible in the study setting. When government restrictions allow, we have undertaken community meetings and promoted the study more widely within the community. The study was further challenged when, due to the impact of the COVID-19 pandemic, Mobenzi, the South African software company being used by the study discontinued its support for mobile data collection at the end of December 2021. After considerable efforts by the study team, data collection was transitioned to REDCap (Richmond, VA; Vanderbilt University).

Given the impacts of the COVID-19 pandemic, we have reflected on the appropriateness of using historical controls to evaluate the effectiveness of the optimised intervention. The experience of lockdown may have changed levels and patterns of sexual activity, particularly of couples who are not living together. This in turn may have changed couples’ perceptions of their HIV risk and their need to know their current HIV status. In KZN province, at the start of the pandemic, use of HIV testing services declined but gradually improved as restrictions eased towards pre-lockdown levels by August 2020 [44]. Specific data regarding provision and uptake of couples HIV testing in KZN during this period are not available, however it is expected that these will have followed a similar pattern, and not be any higher than pre-pandemic low levels [9]. Key characteristics related to HIV risk are measured in the Igugu Lethu study. In analyses, the Igugu Lethu cohort’s baseline characteristics will be compared with the baseline characteristics of the historical controls from the Uthando Lethu study. Therefore, we can adjust analyses for any important differences.

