## Background

South Africa has experienced one of the world’s most severe generalised HIV epidemics. In 2011, HIV prevalence was 29% among resident adults aged 15–49 years in KwaZulu-Natal (KZN) [1]. Between 2004 and 2011 HIV incidence in KZN was 2.63 per 100 person-years (95% CI 2.50 to 2.77) [2], with the majority of new infections occurring within heterosexual partnerships. Current recommendations are that HIV treatment should be started as soon as diagnosis is made [3]. Therefore, regular HIV testing remains crucial to achieving high levels of treatment coverage and the gateway for treatment and prevention pathways (e.g. pre-exposure prophylaxis). South African HIV testing campaigns have increased individual knowledge of HIV status but have not overcome barriers to repeat HIV testing and disclosure of HIV status to sexual partners [4]. Gender-specific concerns about HIV testing and treatment are well documented [5]. Thus, it is important that universal test and treat and treatment as prevention efforts are sensitive to men and women’s relationships with partners and family. In couples HIV testing and counselling (CHTC), couples are counselled, tested and receive their HIV results together [6]. In South Africa, as elsewhere in sub-Saharan Africa, the provision and uptake of CHTC remains low [7]. CHTC accomplishes two important goals. First, knowledge of each other’s HIV status can facilitate risk-reduction behaviour within partnerships via effecting positive changes (e.g., condom use) in sexual behaviour with primary and any concurrent partners. Second, knowledge of HIV status can increase access to treatment and care for HIV-positive individuals, as well as reinforce behavioural choices (e.g., limiting concurrent partners) to stay HIV-negative.

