Between 2012 and 2015, the Uthando Lwethu Study tested the efficacy of an interdependence theory-based behavioural couples-focused intervention to increase participation in CHTC in South Africa among couples who had never tested for HIV together or mutually disclosed their HIV status [8]. Three hundred thirty-two couples were randomised to the intervention arm (168 couples) or the control arm (164 couples). The intervention arm received two group sessions and four couples counselling sessions, focused on problem-solving and communication skills and was highly effective in increasing the proportion of couples that decided to test for HIV together within 9 months after enrolment, (42% v. 12% [*p* < 0.001]) compared to the control group [9]. Concerned that, in a high HIV prevalence and continued HIV incidence setting [10], 58% of intervention couples did not choose to test together during the Uthando Lwethu study, we optimised the Uthando Lwethu intervention using the Person-Based Approach to intervention development and optimisation [11]. The details of the process of optimising the intervention have been published elsewhere [12]. In brief, a qualitative study was conducted with 20 purposively sampled couples who were formerly enrolled in the intervention arm of the Uthando Lwethu Study, and with 5 study staff who delivered intervention components, with the aim of exploring experiences of the intervention and barriers to testing. The past participants sampled included couples who did not attend couples counselling sessions and did not test for HIV together, some couples who attended all couples counselling sessions and tested for HIV together during follow-up, and others who only took up part of the intervention, with or without deciding to test for HIV together. Developing guiding principles and a logic model that showed how the optimised intervention would increase uptake to CHTC ensured that optimisations were grounded in the local context and drew on theoretical constructs [12]. The optimised intervention still involves two group sessions and up to four couples’ counselling sessions but differs from the Uthando Lwethu intervention in session content, involving community members speaking publicly about their HIV testing history and HIV status, and the possibility that the number of counselling sessions provided will be less if the couple engages in couples HIV testing at an earlier point in the intervention.

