### Study objectives

The primary objective of the Igugu Lethu study is to measure the efficacy of our optimised theory-based and culturally appropriate couples-focused intervention on the uptake of HIV testing as a couple. We also have four secondary objectives. First, we aim to investigate the extent to which relationship dynamics are factors in achieving the outcome of couples’ uptake of HIV testing together. Second, we aim to explore whether couples take up other testing opportunities offered during the health screening visit, and the frequency of couples’ health concordance (the same status) for the different tests conducted. Third, we aim to identify operational reasons for failure or success in implementing the intervention and of the study as a whole. Finally, we aim to explore the penile microbiome functional characteristics of male partners and the vaginal microbiome functional characteristics of female partners and concordance in these characteristics within couples.

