### Study design

Igugu Lethu is a prospective cohort study. Figure 2 summarises the study flow, including two stages of recruitment (initial screening and baseline screening) to determine the eligibility of couples to participate in the Igugu Lethu study, and the intervention sessions and follow-up assessments for those enrolled.

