### Intervention

The proposed optimised behavioural intervention consists of up to six sessions (one group session in which couples are initially together and subsequently split into single-gender subgroups, a second single-gender group session, and four couples’ counselling sessions). The intervention is hypothesised to provide information and education around HIV testing and treatment, transform couples’ motivation for looking after their health as a couple rather than as individuals, as well as to improve communication, intimacy and trust necessary for mutual decision-making about behaviours related to sexual risk behaviour and testing for HIV.

Couples will not be reimbursed for the intervention sessions as these are perceived to offer a benefit to couples in and of themselves, and this offers a more feasible set-up to scale-up and implement more widely. This is different to the Uthando Lwethu study which offered reimbursement of ZAR50 (approximately GBP 3.00, as of January 2014) per person per session for all intervention sessions.

#### Group session 1

This first group session will be comprised of a half-day workshop focusing on general health issues in couples, including health conditions assessed at the general couples health screening (blood pressure, diabetes, curable STIs, obesity and HIV). Both partners participate together in the first section of the workshop, with approximately 15–20 couples in each group. Subsequently, the couples will be split into male-only and female-only sub-groups to begin discussing sexual health, family planning, HIV awareness, and benefits and barriers to testing. Community members living with HIV and others who have recently tested HIV negative, and have previously spoken publicly about their HIV testing history and HIV status, will be invited to attend and facilitate a dialogue around couples testing and impact on relationships during the single-gender session.

#### Group session 2

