### Outcomes

#### Primary outcome

The primary outcome measure is the proportion of couples that take up couples HIV testing as part of a health screening visit during study follow-up i.e. within 4 months from the date of the first group session, compared to the equivalent proportion in the intervention arm of the Uthando Lwethu study (historical controls).

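### Baseline adjustment does not answer the historical-control question: calendar period is fully aliased with intervention version, so a difference in uptake cannot be called efficacy without qualification

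*Protocol article*

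**What the plan says.** Study design: "Igugu Lethu is a prospective cohort study". There is no concurrent control. Under Primary outcome, the proportion testing together within 4 months of the first group session is compared with the equivalent proportion in the Uthando Lwethu intervention arm.

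The two periods do not overlap. Background: "Between 2012 and 2015, the Uthando Lwethu Study tested the efficacy". Impact of the COVID-19 pandemic: delays ended up "resulting in study recruitment beginning in December 2020".

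Data analysis makes the primary test an unadjusted chi-square, with logistic regression on baseline characteristics if these differ substantially. The section on the pandemic says that lockdown may have altered sexual activity, perceived HIV risk and the felt need to know one's status. It reports that no specific data on couples testing exist for the period, expects couples testing to be no higher than before, and ends: "Therefore, we can adjust analyses for any important differences".

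The primary objective is to "measure the efficacy of our optimised theory-based and culturally appropriate couples-focused intervention on the uptake of HIV testing as a couple".

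Delivery also changed with the study. Couples are not reimbursed for intervention sessions; the Intervention section notes: "This is different to the Uthando Lwethu study which offered reimbursement of ZAR50" per person per session. Study design mentions some adjustments to recruitment and follow-up for SARS-CoV-2.

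**The concern.** The closing sentence stands as the answer to a question about period, but what it describes is adjustment for baseline covariates. The two coincide only if every relevant change between 2012–2015 and December 2020 onward acts through variables measured at baseline in both studies. The article does not argue this, and nothing in the design could test it.

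At stake is what the primary comparison can support. An unadjusted chi-square against a fixed earlier cohort tests whether the two cohorts differ in uptake. Reading a difference as efficacy of the optimised intervention needs the further assumption that the earlier intervention, delivered again from December 2020, would still have produced about 39%. Drift upward would be credited to the new version; drift downward would hide a real gain.

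**Working it through.** **Inputs.** Control uptake 65/168 = 38.7%, given as 39%; target 55%; 180 new couples, 5% loss (171 left); 5% level. All are in Sample size, accrual, follow-up. The number of sides is not stated; two-sided is assumed.

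**1. The plan's power.** Pooled-variance normal approximation, no continuity correction, with n₁ = 168 and n₂ = 180:

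- p̄ = (168 × 0.39 + 180 × 0.55)/348 = 0.4728
- SE₀ = √[p̄(1 − p̄)(1/168 + 1/180)] = 0.0536
- SE₁ = √[0.39 × 0.61/168 + 0.55 × 0.45/180] = 0.0528
- power = Φ[(0.16 − 1.96 × 0.0536)/0.0528] = Φ(1.04) = 85.1%

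With 171 couples it is 84.2% (control 39%) or 85.6% (control 65/168). The stated figure reproduces, so the sample size is not at fault.

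**2. Aliasing.** Code intervention version as 0 (Uthando Lwethu) or 1 (Igugu Lethu), and era as 0 (2012–2015) or 1 (December 2020 onward). The two columns are identical. The design matrix of intercept, version and era has rank 2 of 3; with a baseline covariate added it has rank 3 of 4. The covariate is estimable, but version and era remain inseparable.

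**3. Effect of drift on the primary test.** Let d be the change in uptake between the periods that has nothing to do with the new version. Set the intervention benefit to zero: 39% in the controls, 39% + d in the new cohort. The chance of a significant result in favour is Φ[(d − 1.96·SE₀)/SE₁], with the standard errors recalculated for each d. For d = +0.10: SE₀ = 0.0533, SE₁ = 0.0530, giving Φ(−0.083) = 0.467. The documents give no value for d, so this range is an assumption.

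| Assumed drift (points) | P(significant improvement), 180 couples |
|---|---|
| −5 | 0.2% |
| 0 | 2.5% |
| +3 | 8% |
| +5 | 15% |
| +8 | 32% |
| +10 | 47% |
| +16 | 85% |

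Exact binomial enumeration agrees to within rounding. With 171 couples, +5, +8 and +10 give 15%, 32% and 46%. The last row equals the planned power, as it must: a 16-point drift looks the same to this test as the target effect.

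**4. Tipping point if the target is met.** Uncorrected chi-square, 99/180 (55%) against a shifted benchmark:

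- 65/168 (38.7%): p = 0.0023
- 74/168 (44.0%): p = 0.041
- 75/168 (44.6%): p = 0.053

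The conclusion changes after a shift of 10 couples, 10/168 = 6.0 points. The margin shrinks for a smaller observed gain: against 65/168, 89/180 (49.4%) is the first significant count (p = 0.044) and 88/180 is not (p = 0.055).

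**The case against.** **The sentence may mean only baseline differences.** The line before it speaks of comparing baseline characteristics, and Data analysis gives the adjustment rule in that scope. The reading is fair, and the article nowhere says outright that period confounding is removed. But on this reading the question that opens the paragraph goes unanswered.

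**Part of a period effect can be adjusted for.** This stands. The pathways named run through sexual behaviour and risk perception, and Baseline survey says both are measured with instruments used in Uthando Lwethu. Only the remainder is beyond reach.

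**Bias may be conservative.** The article expects background couples testing to be no higher than before, and ending session payment might lower attendance. Either could work against the new version. However, the expectation rests on no couples-testing data and concerns background uptake, not uptake among couples given the intervention. Direction is therefore open, and the drift table runs both ways.

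**The limitation is partly disclosed, and sensitivity analyses belong in an analysis plan.** Both are true. The absence of a tipping-point analysis from a condensed article is not the fault raised here; the fault is the inference the article states.

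Stronger readings are tempting but not supported:

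- A reader might infer that treatment policy changed between the studies. The Background says only "Current recommendations are that HIV treatment should be started as soon as diagnosis is made"; it does not say what applied in 2012–2015.
- A reader might infer that recruitment routes were wholly new. Study design calls the strategies similar with some adjustments, the abstract calls them the same, and the earlier routes are not described.
- Ending session reimbursement is a disclosed choice with a scale-up rationale, not an effect of era. It matters only because it changed together with the intervention content.

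**Conclusion.** The point holds as a limit on what adjustment can do and on how the result may be described. Era and intervention version are completely aliased, so logistic regression on baseline characteristics removes only the part of a period effect that acts through variables measured in both studies. Residual period effects and accompanying delivery changes remain in the comparison.

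For size, an assumed upward drift of 5 to 10 points would raise the chance of a false improvement from 2.5% to between 15% and 47%; a 5-point downward drift would cut it to about 0.2%. At exactly 55% uptake, a 6-point shift in the benchmark removes significance. These figures rest on a two-sided 5% test without continuity correction, 168 and 180 couples, and drift values that are assumptions.

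A reader might conclude that a positive result would be a period artefact, or that historical controls make the study uninformative. The documents support neither: they show only that the two explanations cannot be told apart within this design.

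**What to change.** 1. In Impact of the COVID-19 pandemic, limit the closing sentence to baseline characteristics measured in both studies, and add that period and intervention effects cannot be separated in this design.
2. Pre-specify a tipping-point sensitivity analysis: shift the 65/168 benchmark in both directions in small steps, repeat the primary test, and report the shift at which the conclusion changes. Present uptake by intervention round as descriptive support. It can show variation within the new cohort but cannot measure change since 2012–2015.
3. Word the primary conclusion as higher (or lower) uptake than the historical cohort, reported with the tipping point, rather than as efficacy without qualification. Align the primary objective with this.

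The cost is a few sentences, a short analysis on data the study will already hold, and a more cautious conclusion. No further couples are needed, and the design and sample size stay as they are.

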## Discussion

By strengthening communication and functioning within the relationship, both the Igugu Lethu and Uthando Lwethu studies aim to transform the motivation of individual partners from a focus on their own health to shared health as a couple [12]. The Igugu Lethu study aims to achieve a 40% higher proportion of couples testing for HIV together than the Uthando Lwethu study. The optimised intervention has four new aspects: (i) community members speak publicly about their HIV-testing history, HIV status, and how testing impacted their relationships as a starting point for group discussion around couples testing; (ii) couples are split into separate single-gender groups earlier than in the Uthando Lwethu study. This provides more time in ‘safe’ spaces to open up and discuss health and relationship issues, prepare themselves for the counselling sessions, thereby priming the couple to gain greater benefit from the counselling process and feel more ready to test; (iii) greater attention is given to assisting couples to understand the consequences of testing, change outcome expectancies, and manage negative emotions around HIV testing. In the counselling sessions, couples will practise their communication and problem-solving skills to discuss HIV-specific issues in their relationship. We anticipate that these relationship strengthening efforts will also have long term benefits for the couple, for example, reducing the risk of IPV; (iv) participants’ knowledge of adult health is broadened to include sexually transmitted infections and the interrelationships between weight, BMI and non-communicable diseases such as diabetes and hypertension in the first group session. In addition to standard CHTC, participants are offered an opportunity to test for other health conditions including STIs.

Igugu Lethu study findings regarding uptake levels of other health screening by couples that have chosen to take up CHTC, can inform differentiated HIV testing strategies [45], differentiated HIV service delivery [46] and taking such interventions to scale [47]. Offering health screening outside of the clinic setting may also mean that men who have been previously hard-to-reach for HIV testing and care could be reached as male partners [16, 48]. The acceptability and feasibility of asking participants, in the context of a couple, to privately self-sample for STI testing will also be important for future research and practice. Providing STI results to couples is also an opportunity for treating asymptomatic cases and promoting reproductive health, facilitating partner treatment and reducing onward STI transmission.

The main hypothesis of the Igugu Lethu study is that our optimised couples-focused behavioural intervention and offering a broader health screening alongside couples HIV testing will increase demand for CHTC. CHTC has already been shown to be cost-effective and to contribute to preventing new HIV infections [49], an outcome that is highly desirable in populations with high HIV prevalence.

